### Allocation and randomization

3.3

A total of 72 eligible patients are allocated to receive either a combination of mechanical (ADM) and biological (cHBM + SAB) augmentation after RC repair or mechanical augmentation with ADM alone, in a 1:1 ratio (36 patients for each group of treatment) based on a computer-generated randomization.

The randomization list is created using an online randomization list generator^2^ with a permuted block of variable length from 2 to 6. Enrolled patients are randomly assigned to the massive RC repair augmented with autologous cHBM, SAB and ADM arm (group B) or to the ADM augmentation alone (group A), as comparator arm, following a pre-determined randomization list. Patients and outcome assessors are blinded, while the surgeon knows the group assignation of the patient the day of surgery, opening a dedicated closed envelope.

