### Statistical analysis

3.12

To identify the minimum patient sample size, an *a priori* power analysis is performed (G*Power 3.1.9.6v software, University of Kiel, D) based on a previous study (2), which used the same ADM on *n* = 5 patients, obtaining a re-tear rate of 40%. Furthermore, Cai et al. (24) obtained a re-tear rate of 13.7% by combining the suture with orthobiological augmentation. The hypothesis of the present study was that the addition of orthobiologicals would result in a re-tear rate of 10%, thus yielding an OR value of 6.

By considering an odds ratio (OR) = 6.0 for re-tear rate between ADM-orthobiologics and ADM alone, 95% confidence and 0.80 power (Fisher’s exact test, onetail) *n* = 36 for both groups is computed. This patient size considers 20% of drop-out patients.

All demographics, clinical, MRI, biological, biomechanical, histological, follow up clinical data are recorded in the electronic dataset for further statistical analysis. The statistical analysis of the results is conducted using SPSS/PC + Statistics TM (SPSS Inc., United States) or the R software (R Core Team, 2021^3^) and the related packages necessary for conducting the analysis such as ggplot2 (25) for graphical data representation. A *p*-value < 0.05 is considered statistically significant.

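### Minor arithmetic error: 36 per arm does not quite cover the stated 20% drop-out at 0.80 power (about 0.78–0.79 remains)

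*Protocol article*

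**What the plan says.** The sample-size reasoning is in section 3.12 (Statistical analysis) of the protocol article.

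- **Control rate (ADM alone):** taken from a previous series of five patients, "obtaining a re-tear rate of 40" per cent.
- **Rate under the combination:** the hypothesis is that "the addition of orthobiologicals would result in a re-tear rate of 10" per cent, "thus yielding an OR value of 6".
- **Error rates and test:** "95% confidence and 0.80 power", with Fisher's "exact test, onetail".
- **Result:** 36 in each group, followed by the sentence at issue: "This patient size considers 20% of drop-out patients".

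Section 3.3 (Allocation and randomization) carries the number forward: "A total of 72 eligible patients are allocated", "in a 1:1 ratio (36 patients for each group of treatment").

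The article prints neither the size before the drop-out allowance nor the formula used to make the allowance.

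**The concern.** The sentence on drop-out, read with the power statement just before it, tells the reader that the trial keeps 0.80 power after losing one patient in five. All the inputs needed to test that claim are printed.

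The usual slip is to multiply the required number by 1 + d, where d is the drop-out proportion, instead of dividing by 1 − d. Multiplying always gives too few patients, because the loss is taken from the enlarged number, not from the required one.

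The primary outcome is read on the 12-month MRI (sections 3.7.1 and 3.8), so a patient without that scan has no observed primary outcome. If the allowance is too small, the power at the planned loss is lower than readers, the funder and the ethics committee are told.

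**Working it through.** **Inputs, all from section 3.12 (allocation from section 3.3).** p_A = 0.40 (ADM alone); p_B = 0.10 (ADM plus orthobiologics); one-tailed Fisher's exact test; α = 0.05, from 95% confidence; target power 0.80; 1:1 allocation; drop-out d = 0.20; stated size 36 per arm.

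**Step 1: the odds ratio.** (0.40/0.60) / (0.10/0.90) = 6.0. This matches the plan.

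**Step 2: exact power.** For n_A and n_B evaluable patients,

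power = Σ Bin(x; n_A, 0.40) · Bin(y; n_B, 0.10),

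summed over all pairs (x, y) whose one-tailed Fisher p-value is at most 0.05.

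| Evaluable, ADM alone / combination | Power |
|---|---|
| 28 / 29 | 0.778 |
| 29 / 28 | 0.789 |
| 29 / 29 | 0.781 |
| 30 / 30 | 0.801 |
| 36 / 36 | 0.879 |

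The smallest equal-arm size that reaches 0.80 is 30.

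**Step 3: reproduce the stated 36.**

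- 30 × (1 + 0.20) = 36, which matches exactly.
- Other formulas were tried with the same rates. The one-sided normal approximation needs 25 per arm (32 after dividing by 0.8, 30 after multiplying by 1.2). The one-sided formula with continuity correction and the two-sided normal approximation each need 32 (40 or 39). The two-sided formula with continuity correction needs 38 (48 or 46). None gives 36 after inflation.
- A two-sided Fisher test with no drop-out allowance also needs 36 (power 0.8004), but the text states one tail and an allowance.

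So 30 × 1.2 is the likely route. It remains an inference.

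**Step 4: the allowance that covers 20% loss.** 30 / (1 − 0.20) = 37.5, rounded up to 38 per arm and 76 in total. Check: 38 × 0.80 = 30.4, which leaves 30 per arm.

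**Step 5: what 36 per arm delivers.**

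- 36 × 0.80 = 28.8 per arm, or 72 × 0.80 = 57.6 in total. The nearest whole-number cases are 28 with 29, and 29 with 29, so power is 0.778 to 0.789.
- Averaging over random 20% loss in each arm gives about 0.785.
- Shortfall: 0.80 − 0.789 = 0.011 to 0.80 − 0.778 = 0.022.

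**Step 6: the loss that 36 per arm does cover.** 36 − 30 = 6 per arm, and 6/36 = 16.7%.

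**Step 7: the optional test.** A one-sided Boschloo test at 0.05 has a maximum size of 0.047–0.048 at these sample sizes. Its power is 0.835 (28/29), 0.841 (29/28) and 0.858 (29/29).

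**The case against.** The best defence has three parts.

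**The gap is very small.** It amounts to 2 patients per arm and about 1.5 points of power. With no loss, power is 0.879, and up to 16.7% loss in each arm the claim holds. The uncertainty in the inputs is far larger, since the 40% control rate is 2 of 5 patients. This stands, and it is why the point is minor.

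**The sentence may promise less.** To say that a size considers 20% drop-out could mean only that 20% was added to the required number. That reading is possible. But a drop-out allowance exists to preserve the stated power at the stated loss, and this one does not quite do so.

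**The route to 36 is not printed.** This also stands, so the text should be called consistent with 30 × 1.2 and no more. The result does not depend on the route: 36 less 20% is 28.8, and at the nearest whole-number sizes the plan's own test falls below 0.80.

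A reader might also infer something worse. Neither of the following is supported.

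- **Power of 0.762.** This is the value at 28 per arm, but 28/28 means 16 of 72 lost, which is 22.2% and not 20%.
- **Power of 0.66–0.68.** These are two-sided values at 28 and 29 per arm. The plan states one tail. Whether one tail is appropriate is a separate question and does not bear on the drop-out arithmetic.

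**Conclusion.** The point holds as a minor arithmetic error. On the plan's own rates, test and α, 0.80 power needs 30 evaluable patients per arm. Covering 20% loss would take 38 per arm, and 36 per arm leaves power of about 0.78–0.79. The shortfall is about 1 to 2 points, equivalent to 4 patients (76 − 72, or 5.6% of 72).

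This rests on three assumptions: α = 0.05 one-sided, as 95% confidence with one tail implies; drop-out means no evaluable 12-month MRI; and losses are split about evenly between the arms.

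It does not follow that the trial is seriously underpowered or has to be enlarged. No estimate and no type I error rate is affected. Nor do the documents establish how the authors reached 36.

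**What to change.** Keep 72 patients and correct the statement in section 3.12. Suggested wording:

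*With re-tear rates of 40% and 10%, a one-tailed Fisher's exact test and α = 0.05, 0.80 power requires 30 evaluable patients per arm. Randomizing 36 per arm allows for up to 6 losses per arm (16.7%). At 20% loss, power is about 0.78–0.79.*

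This costs one or two sentences and no patients. If the sponsor prefers to keep the 20% claim as it stands, the size that supports it is 38 per arm, 4 more patients in total.

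Optionally, prespecify a one-sided Boschloo unconditional exact test for the primary comparison. It keeps size at or below 0.05 and gives power of about 0.83–0.86 at 28–29 per arm, so 72 patients would cover 20% loss. This is not needed to correct the error. Section 3.12 names Fisher's test only within the power calculation, and the primary test may be fixed in an analysis plan that is not shown. If the option is taken, it should be settled before any outcome data are unblinded, and the power statement should be rewritten for the new test.

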### Data monitoring

3.13

A central project data manager is tasked to perform data quality control on all collected data. An *ad interim* report and a final report are foreseen, to be submitted to the Ministry of Health who funded the project. A further project auditing is performed by another independent entity of the Institution, the Clinical Trial Center. The final study report is also sent to the Ethic Committee.

## Discussion

4

This is the first randomized, double-blind, and controlled trial comparing the efficacy of human acellular dermal matrix (ADM) alone or combined with humeral bone marrow aspirate concentrate (cHBM) and subacromial bursa (SAB) for re-tear prevention in treatment of RC Repair. Patients are analyzed using Patient Reported Outcome Measures (PROMs), objective measures and MRI examination, and biomarker evaluation. Orthobiologics and ADM are analyzed for all baseline characteristics, in terms of number of cells, regenerative potentials and biomechanical competence, and correlated with clinical outcomes.

This study can clarify the benefits and limitations of the newly proposed dermal allograft for RC tears and the role of associated orthobiologics augmentation, providing precious indications for the clinical practice.
